## Choice of individuals to include in the analyses

ITT population: all included patients according to the period assigned by the randomization to the center, regardless of the strategy effectively received by the patient.

Per protocol population: all included patients without major protocol deviation:

- No respect of selection criteria,
- No respect of strategy assigned by randomization (cross-over for example),
- Missing value for the principal criteria,
- Other major protocol deviation identified during data review and freezing of data base.

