### Research end date (D30)

The end of study visit will be at 30 day. The in-hospital mortality will be truncated at 30 days.

- If the patient is still hospitalized: the follow-up visit will consist of a hospital visit and a chart review to ascertain the primary endpoint.
- If the patient is not still hospitalized: the follow-up visit will consist of a phone interview topatient/ trustworthy person / family member / close relative. The family practitioner of the patients will be sought for information in case the patients/relatives cannot be reached.

If follow up is impossible, the investigators or CRT will contact the city hall and administrative service of his hometown to seek for possible death.

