# EFFICACY ASSESSMENt

## Description of parameters for assessing efficacy endpoints

The primary endpoint (days alive and out of hospital at day 30) will be measured at the end of the 30 days follow up period, either by hospital visit, phone interview, and medical chart review. Vital status, date of death and date of discharge will be collected.

A death during the follow up period will correspond to 0. An ED visit will correspond to “one day” at the hospital.

For example, a patient not admitted (at day 0), with no return visit to the hospital, and alive at day 30 will have 30 days alive and out of hospital.

A patient who is admitted (at day 0) and stays 8 days in the hospital before being discharged and have no readmission and no return visit to the ED would have a “22 days alive and out of hospital at 30 days”.

A patient that is admitted and die at 13 days, either at home or in hospital will have 0.

A patient that is admitted for 10 days, discharged home for 5 days then admitted at day 16 for 15 days will have 5 days alive and out of hospital (namely day 11, 12, 13, 14 and 15).

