## Anticipated methods and timetable for measuring, collecting and analyzing the efficacy data

- In-hospital mortality will be obtained from hospital data base (Mediweb, Gilda, or Orbis) and phone interview with the last known ward of hospitalization of the patient. In case of transfer to another hospital, this data will be collected either by phone interview or hospital visit if necessary.
- 30 day all-causes mortality rate: same as above for patient still in hospital at day 30, phone call to the patients, relatives, or GP if not.
- Cardiovascular related 30 day mortality. Adjudicated by an adjudication committee (see below) as to whether the death has been mainly caused by a cardiovascular issue.
- Length of stay in hospital and changes of more than 2 fold in creatinine level from hospital database (CleanWeb, MediWeb, Gilda or Orbis)
- Efficacy data will be analyzed at the end of the study after data review and freezing of data base.

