## Principal criterion analysis

The number of days alive and out of hospital will be calculated based on date of admission, vital status, date of death and date of discharge will be collected. A death during follow-up will correspond to 0. An ED visit will correspond to “one day” at the hospital.

The number of days alive and out of hospital will be analysed using a linear regression mixed model with a random effect for each cluster, considered fixed effects will be: strategy and, for the stepped wedge design, time representing each step. In case of non-normality distribution of the interest variable, a transformation could be realized.

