## Secondary evaluation criteria

In hospital mortality, all causes mortality at 30 days and cardiovascular mortality at 30 days will be compared between groups by using Pearson's chi-square test or Fisher exact test.

If possible, generalized linear regression mixed model with Poisson distribution will be performed. If the number of events is sufficient, generalized linear regression mixed model using logit link will be performed.

The length of stay in hospital in days will be compared between the two periods by using Student t-test or Wilcoxon rank-sum test as needed. If possible, a linear regression mixed model will be performed. A random effect for each cluster will be considered and considered fixed effects will be: strategy and, for the stepped wedge design, time representing each step. In case of non-normality distribution of the interest variable, a transformation could be realized.

Percentage of patients with a change of more than 2 fold in creatinine between inclusion and 30 days will be compared between groups by using Pearson's chi-square test or Fisher exact test. If possible, generalized linear regression mixed model with Poisson distribution will be performed. If the number of events is sufficient, generalized linear regression mixed model using logit link will be performed.

Second analysis will be performed on the per protocol population.

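### Dropping patients with a missing primary endpoint from the whole per-protocol set can remove known survivors but never a known death; limit the exclusion to the primary endpoint

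*Protocol*

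**What the plan says.** - **Per-protocol set (13.9).** The protocol defines one set: "Per protocol population: all included patients without major protocol deviation". Its list of deviations covers eligibility, strategy received, other major deviations found at data review, and "Missing value for the principal criteria".
- **Use of the set (13.3).** The section on secondary criteria ends with "Second analysis will be performed on the per protocol population". Earlier in that section, "In hospital mortality, all causes mortality at 30 days and cardiovascular mortality at 30 days will be compared between groups", followed by length of stay and creatinine.
- **Scoring of death.** Section 9.1 states "A death during the follow up period will correspond to 0"; section 13.2 states "A death during follow-up will correspond to 0".
- **Follow-up.** Patients still in hospital at day 30 are assessed by visit and chart review (6.1). Where follow-up fails, the investigators or technicians "will contact the city hall and administrative service of his hometown to seek for possible death". Section 8.1 asks that a lost patient at least be classified as alive or dead.
- **Source of other secondary outcomes (9.2).** "Length of stay in hospital and changes of more than 2 fold in creatinine level from hospital database".
- **Missing data (13.7).** A missing primary value is scored 0 days in both periods. Other missing data are left as missing.

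**The concern.** A missing outcome says nothing about whether the patient was eligible or received the assigned strategy, which is what a per-protocol set is meant to capture. Here the rule is also tied to the outcome. A patient who cannot be reached stays in the set if a death is traced, because that patient then scores 0. If the patient is established to be alive but the days in hospital cannot be reconstructed, the patient leaves the set.

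Because there is only one per-protocol set, the removal carries over to every endpoint analysed in it. Two things are at stake. Per-protocol mortality may be computed on a set from which some known survivors have been taken out. Length-of-stay and creatinine values already held in hospital databases may go unused because a different variable is missing.

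**Working it through.** **Inputs**
- N = 500 patients and a 10% non-evaluable allowance (13.4). The plan's total agrees with its own allowance: 454 × 1.10 = 499.4, given as 500. No stated figure is in dispute.
- 30-day mortality of 10% (2.1 and 2.6), taken as D = 50 known deaths.
- M = number with a missing primary endpoint. The protocol does not forecast M. I use the 10% allowance as an assumption (M = 50), with 5% and 2% as alternatives.
- a = share of those M patients known to be alive. The protocol gives no value, so I show the range 0 to 1.

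**Step 1: per-protocol against ITT mortality.** No known death is among the M patients, and unknown vital status is not imputed (13.7). Setting other deviations aside:
- per-protocol mortality = D / (N − M)
- ITT mortality among patients with known status = D / (N − M(1 − a))

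| Missing | Per-protocol | ITT, a = 1 | ITT, a = 0.5 | ITT, a = 0 |
|---|---|---|---|---|
| 10% (M = 50) | 50/450 = 11.1% | 50/500 = 10.0% | 50/475 = 10.5% | 50/450 = 11.1% |
| 5% (M = 25) | 50/475 = 10.5% | 50/500 = 10.0% | 50/487.5 = 10.3% | 50/475 = 10.5% |
| 2% (M = 10) | 50/490 = 10.2% | 50/500 = 10.0% | 50/495 = 10.1% | 50/490 = 10.2% |

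The excess due to the rule is at most 1.1 points at 10% missing. It vanishes when none of the dropped patients has known status, because they are then absent from both analyses.

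**Step 2: direction relative to true mortality.** Suppose 50 patients truly die and a share q of the 50 dropped patients are among them, untraced. Per-protocol mortality is (50 − 50q)/450: 11.1% at q = 0, 45/450 = 10.0% at q = 0.10, and 40/450 = 8.9% at q = 0.20. The sign depends on mortality among the dropped patients.

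**Step 3: comparison between periods.** With equal missingness and equal mortality, both periods shift alike: at 5% missing each, 0.10/0.95 = 10.5% in both. A false difference needs unequal missingness. For illustration only, with no treatment effect and all dropped patients known alive, 5% against 15% gives 0.10/0.95 = 10.5% and 0.10/0.85 = 11.8%. That is 1.2 points, or a risk ratio of 0.95/0.85 = 1.12. With about 25 deaths per group, the standard error of the log risk ratio is about 0.27, so ln(1.12) = 0.11 is about 0.4 standard errors.

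**Step 4: length of stay.** Assume 80% admitted, a gamma-distributed stay with median 10 days capped at 30, and missingness only among patients discharged alive. The mean is then 9.72 days in all patients and 9.84 in the per-protocol set, a shift of about 0.1 day. The exact value depends on the assumed shape. No size is available for creatinine.

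**Step 5: primary endpoint.** Take full adherence, 14 against 17 days (13.4), and 10% missing unrelated to outcome. ITT with zeros gives 0.9 × 14 = 12.6 and 0.9 × 17 = 15.3, a difference of 2.7 days. Per-protocol on observed values gives 17 − 14 = 3.0 days. The gap comes from the zero imputation in 13.7, not from adherence.

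**The case against.** **Scope.** The sentence in 13.3 is short and could simply contrast with 13.1, which makes the principal analysis ITT. If the per-protocol analysis concerns only the primary endpoint, the points on mortality, stay and creatinine fall away. Its place at the end of the secondary-criteria section favours the wider reading but does not settle it.

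**Who is missing.** A reader might infer that only patients discharged alive and not reached can be missing. Section 8.1 also allows patients to leave or be withdrawn at any time, including in hospital, and 9.2 notes that outcomes after transfer need separate tracing. In addition, finding no death at the town hall does not by itself prove that a patient is alive, so some dropped patients will have unknown status and are lost to the ITT mortality analysis too. This stands, and it is why the excess runs from zero to 1.1 points.

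**Stronger readings.** A reader might infer that per-protocol mortality is simply too high, or that a false treatment effect on mortality follows. Step 2 shows that the first is not certain. The second needs missingness that differs by period; the protocol gives the same day-30 follow-up in both periods and shows no such difference.

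**Zero imputation.** A reader might also want the per-protocol primary analysis to use the same zeros as ITT. In Step 5 that would carry the shrinkage from 3.0 to 2.7 days into the per-protocol result, so it is not a clear gain.

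**What remains.** None of this defends applying the exclusion to endpoints whose values are known.

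**Conclusion.** The point holds in a limited form and is minor. As written, the exclusion can remove known survivors but no known death, and it discards secondary outcomes that can be known. Whether it affects the secondary endpoints depends on reading 13.3 as covering them. On that reading, per-protocol mortality exceeds ITT mortality by 0 to 1.1 points at 10% mortality and an assumed 10% missing, according to how many of the dropped patients are known to be alive. The expected effect on length of stay is small. The documents support neither a definite direction of bias against true mortality nor a spurious difference between periods. The ITT analysis keeps all included patients and is untouched, so the trial's main conclusion does not depend on this. It is a free improvement, not a flaw that threatens the result.

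**What to change.** 1. In 13.9, state that a missing primary endpoint excludes a patient only from the per-protocol analysis of the primary endpoint.
2. For secondary endpoints, define the per-protocol set by eligibility, strategy received and other major deviations. Include every such patient whose value for that endpoint is known (vital status, index stay, creatinine).
3. Do not require zero imputation in the per-protocol analysis of the primary endpoint. When it is set beside ITT, note that the two differ in missing-data handling as well as in adherence.

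The cost is one amended line in 13.9 and one sentence in 13.3 or the SAP. No new data and no extra patients are needed.

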# QUALITY **CONTROL AND ASSURANCE**

Every clinical study managed by AP-HP is ranked according to the projected risk incurred by the study participants using a classification system specific to AP-HP-sponsored clinical trials.

## General organization

The sponsor must ensure the safety and respect of individuals who have agreed to participate in the study. The sponsor must have a quality assurance system for monitoring the implementation of the study at the research centers.

The sponsor will establish a system for opening the research centers and may also implement a data quality control system.

The sponsor shall appoint Clinical Research Associates (CRA) whose primary role is to carry out regular follow-up visits at the study sites, after completing their initial visits.

The purpose of monitoring the study, as defined in the Good Clinical Practices (GCP section 5.18.1), is to verify that:

• the research subjects are safe, protected and their rights are being met

•the data being recorded is accurate, complete and consistent with the source documents

•the study is carried out in accordance with the current version of the protocol, with GCP and with all statutory and regulatory requirements.

### Strategy for site opening

The strategy for opening the centers will be determined before the research begins.

Opening visit will be carried out by the local investigator and at least one member of the steering committee and one member of URC-Est. ED physicians will be invited to participate in the opening session in each center. A similar visit will occur at the time of the period switch, with the presence of one member of URC-Est, one member of the steering committee and the local investigator.

### Data quality control

For this study, the appropriate monitoring level has been determined based on the complexity, the impact and the budget for the study. Therefore the sponsor, in agreement with the coordinating investigator, has agreed on a logistical score and impact and the corresponding study monitoring level of: **minimal** level.

A Clinical Research Associate (CRA) appointed by the sponsor will be responsible for the proper running of the study, for collecting, documenting, recording and reporting all handwritten data, in accordance with the Standard Operating Procedures applied within the DRCI.

The investigator and the members of the investigator's team agree to make themselves available during regular Quality Control visits by the Clinical Research Associate.

During these visits, the following elements will be reviewed:

- written consent
- compliance with the study protocol and its procedures
- quality of the data collected in the case report forms: accuracy, missing data, consistency of the data with the "source" documents (medical files, appointment books, original copies of laboratory results, etc.)

## Case report forms

All information required by the protocol must be entered in the case report forms. The data must be collected as and when they are obtained, and must be written clearly and legibly. Any missing data must be coded.

Every site will have access to the electronic case report forms via a web-based data collection system. Investigators will be given instructions for using this tool.

Using on-line case report forms means the CRA can view the data quickly and remotely. The investigator is responsible for the accuracy, quality and relevance of all the data. In addition, there are consistency checks to ensure the data are verified immediately upon being entered. The investigator must validate any changes to the values in the case report form. An audit trail will be kept of all changes. A justification can be added when applicable, as a comment.

A print-out, authenticated (signed and dated) by the investigator, will be requested at the end of the research. The sponsor will keep the original. The investigator must keep a copy.

## Management of non-compliances

Any events that occur as a result the investigator or any other individual involved in conducting the study failing to comply with the protocol, standard operating procedures or statutory and regulatory requirements must be recorded in a declaration of non-compliance and sent to the sponsor.

The sponsor has its own procedures for managing these non-compliances.

## Audits

The investigators agree to accept the quality assurance audits carried out by the sponsor as well as the inspections carried out by the competent authorities. All data, documents and reports may be subject to regulatory audits. These audits and inspections cannot be refused on the grounds of medical secrecy.

An audit can be carried out at any time by [independent individuals appointed by the sponsor.](http://www.chusa.jussieu.fr/urcest/sous_cadre.php?fich=Lexique/new_index.php?isphp=0&fich=EC/legislation/DispositionslegislativesPromoteur.htm) The aim of the audits is to ensure the quality of the study, the validity of the results and compliance with the legislation and regulations in force.

The persons who manage and monitor the study agree to comply with the sponsor's audit requirements.

The audit may encompass all stages of the study, from the development of the protocol to the publication of the results and the storage of the data used or produced as part of the study.

## Principal Investigator's declaration of responsibility

Before starting the study, each investigator will give the sponsor’s representative a signed and dated copy of his/her most recent curriculum vitæ, produced within the past year, and RPPS number (RépertoirePartagé des Professionnels de Santé, Collective Database of Health Professionals). The CV must describe any previous participation in clinical research and related training.

Each investigator will agree to comply with legislation and to conduct the study in line with regulations, in accordance with the Declaration of Helsinki.

The Principal Investigator at each participating site will sign a declaration of responsibility (standard DRCI document) which will be sent to the sponsor's representative.

The investigators and their co-workers will sign a delegation form specifying each person's role and must supply their CV.

# ETHICAL AND LEGAL CONSIDERATIONS

## Methods for informing and obtaining consent from the research participants

*This is a cluster stepped wedge randomised trial, in other words randomization is performed at the hospital level and concerns the switch from control period (no intervention in care) to interventional period (focus on standard care recommendations). The informed consent of the patients will be required to collect his in-hospital data in the eCRF, and the 30-day follow up.*

In accordance with Article L.1122-1-1 of the Code de la Santé Publique - CSP (French Public Health Code), no Minimal Risk and ***Constraints*** research can be carried out on a person without his/her free and informed consent, obtained expressly after the person has been given the information specified in Article L.1122-1 of said Code.

The person will be given a reflection period between receiving the information and being asked to sign the consent form.

**If the patient is alert and considered capable of giving consent by the physician in charge:**

After screening, the emergency physician will inform the patient on the aim and details of the study.

In accordance with Article L.1122-1-1 of the French Public Health Code, no research can be carried out on a person without his/her free and informed consent, obtained in writing after the person has been given the information specified in Article L.1122-1 of said Code.

In addition, the investigator will specify in the research participant’s medical file the methods used for obtaining their consent [*or the consent of any other person, in the cases described in Articles L.1122-1-1 to L.1122-2 CSP*] as well as the methods used for providing information with a view to obtaining consent. The investigator will retain the original signed and dated consent form The information sheet and a copy of the consent form, signed and dated by patient and by the investigator or the doctor representing the investigator, will be given to the individual.

**If the person is unable to give his or her written consent:**

The consent may be obtained, in descending order of priority, from a legal representative, family member or a close relative. These persons must have no connection whatsoever to the investigator or the sponsor.

In accordance with Article L.1122-1-3, since this trial focus on an emergency condition with high mortality and morbidity, the signature of the consent by the patient can be obtained after the treatment has been started. The patient’s free and informed written consent will be obtained as soon as the clinical condition of the patient allow it by the investigator, or by a doctor representing the investigator.

if the patient is unable to provide his written informed consent and in the absence of the trustworthy person, next of kin or close relative : a procedure for inclusion in the study in emergency situation will be applied (article L1122-1-2 of the French Public Health Code). In this case, continuation-of-care consent for the study will be signed by the patient (if need be by trustworthy person, family member or close relative) as soon as possible, according to French Law (article L1122-1-2 of the French Public Health Code).

**If the patient is a protected adult,** in accordance with L.1122-2, the consent will be sought from his legal guardian.Furthermore, in case of death of the patient included in emergency situation, data collected will be used and conserved as part of research.

## Prohibition of concomitant clinical studies participation and exclusion period after the study, if applicable

Whilst participating in this trial, subjects may not take part in any other clinical study without first speaking to the doctor in charge of this trial. A participation in a non-interventionnal, observational study can be allowed during the trial. There is no exclusion period after the participation of the subject.

